## Abstract

**Background**: Cryptococcal meningitis is a leading cause of death in HIV-infected patients. International treatment guidelines recommend induction therapy with amphotericin B and flucytosine. This antifungal combination is most effective, but unfortunately flucytosine is expensive and unavailable where the burden of disease is greatest. Where unavailable, guidelines recommend treatment with amphotericin and fluconazole, but this is less effective, with mortality rates of 40-50%. Faster rates of clearance of yeast from cerebrospinal fluid (CSF) are associated with better outcomes - improving the potency of antifungal therapy is likely to be an effective strategy to improve survival. Tamoxifen, a selective estrogen receptor modulator used to treat breast cancer, has anti-cryptococcal activity, appearing synergistic when combined
*in vitro *with amphotericin, and fungicidal when combined with fluconazole. It is concentrated in the brain and macrophages, off-patent, cheap and widely available. We designed a randomized trial to deliver initial efficacy and safety data for tamoxifen combined with amphotericin and fluconazole.

**Method**: A phase II, open-label, randomized (1:1) controlled trial of tamoxifen (300mg/day) combined with amphotericin (1mg/kg/day) and fluconazole (800mg/day) for the first 2 weeks therapy for HIV infected or uninfected adults with cryptococcal meningitis. The study recruits at Cho Ray Hospital and the Hospital for Tropical Diseases, Ho Chi Minh City, Vietnam. The primary end point is Early Fungicidal Activity (EFA-the rate of yeast clearance from CSF), over the first two weeks of treatment. 50 patients will be recruited providing ≈80% and 90% power to detect a difference in the EFA of -0.11 or -0.13 log10CFU/ml/day, respectively.

**Discussion:** The results of the study will inform the decision to proceed to a larger trial powered to mortality. The size of effect detectable has previously been associated with reduced mortality from this devastating disease. Particular side effects of interest include QT prolongation.

**Trial registration**: Clinicaltrials.gov
NCT03112031 (11/04/2017)

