### Randomization

Randomization will be 1:1 to either Tamoxifen augmented or standard antifungal therapy. Block randomization with stratification by hospital of enrolment and by HIV infection status, and variable block sizes of 4 and 6, respectively, will be used to assign subjects to treatment. The randomization list will be generated according to OUCRU standard operating procedures. In brief, the Research Biostatistician will set up statistical code to generate the randomization list and transfer it to the central Study Pharmacist. The Study Pharmacist will change the random seed, i.e. the initialization of the random numbers generator, in the statistical code in order to blind the Research Biostatistician and then run the code to prepare the final randomization list for treatment preparation. The randomization list will be password protected and stored on a secure server to which only the Study Pharmacist has access.

Based on the randomization list, the central Study Pharmacist will generate identical sealed treatment packs for each study ID and distribute them to the sites in batches as required. All treatment packs will be identical in appearance and will contain either Tamoxifen and fluconazole or fluconazole alone. Each pack will contain sufficient fluconazole for the first 2 weeks of treatment. Enrolment logs specific to each ward will be used to assign patients to the next available sequential number and corresponding sealed treatment pack.

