## Statistics

### Sample size and power considerations

Sample size considerations were based on simulation using data from two previously published trials in cryptococcal meningitis conducted in Vietnam
^8,
9^: 96 patients from the BK trial (all recruited at HTD) with at least one quantitative fungal count measurement randomized to amphotericin B plus fluconazole, and 97 randomized to amphotericin B plus flucytosine; plus 49 patients from the CryptoDex trial recruited at HTD or Cho Ray Hospital randomized to placebo (all of these received antifungal treatment with amphotericin B plus fluconazole).

The first set of simulations assumed that the Tamoxifen group was associated with a similar effect on Early Fungicidal Activity (EFA) as amphotericin B plus flucytosine. For sample sizes ranging from 15-30 patients per group, we repeatedly sampled patients from both included BK study arms of that size with replacement, analyzed them, i.e. compared EFA between the two groups, and then determined the proportion of significant results (i.e. the estimated power).

For the second set of simulations, the control group consisted of the combined 145 patients from the BK study and 04CN receiving amphotericin B plus fluconazole. For assumed EFA treatment effects ranging from -0.16 to -0.10 log
_10_CFU/ml per day faster declines in the intervention group, we generated hypothetical intervention group data by simulating this treatment effect on top of the observed fungal count measurements for patients receiving amphotericin B plus fluconazole. Power was then determined based on resampling-based simulation as for the first set of simulations.

Estimated power was based on 10 000 repetitions of each simulation experiment. Estimating EFA based on a mixed model accounting for the detection limit of fungal count measurements was not feasible because this would require excessive computing time. Thus, we used a simple mixed model ignoring the detection limit for the simulations instead but removed values after the first undetectable (zero) fungal count measurements and kept the first fungal count of zero only if it lead to a steeper estimated least-squares decline for that patient compared to omitting the measurement.

Results for both sets of simulations are shown in

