Figure 3. Based on the first simulation study, n=25 subjects per group provide approximately 80% power to detect a difference in EFA of similar size as the difference between amphotericin B plus fluconazole and amphotericin B plus flucytosine observed in the BK study. Based on the second simulation study, n=25 subjects per group provide 80% and 90% power to detect a difference in EFA of -0.11 or -0.13 log10CFU/ml/day, respectively. We consider that this size of effect is likely to deliver a clinical benefit. All simulations were performed using
R software version 3.2.2
^59^.

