## Analysis of the primary endpoint: early fungicidal activity (EFA)

All recorded longitudinal quantitative fungal count measurements up to day 17 (allowing for some delays in the day 14 measurements) will be included in the analysis. EFA will be modeled based on a linear mixed effects model with longtitudinal log
_10_-CSF quantitative culture fungal counts as the outcome, interaction terms between the treatment groups and the time since enrolment of the measurement as fixed covariates and random patient-specific intercepts and slopes. The lowest measurable quantitative count is 5 CFU/ml and values below the detection limit (which correspond to recorded values of 0) will be treated as <4.5 CFU/ml, i.e. non-detectable measurements will be treated as left-censored longitudinal observations in the analysis as we have done previously
^8^.

Based on this model, EFA will be compared between the two treatment arms in all patients (intention to treat), in the per-protocol population, and subgroups defined by HIV status (uninfected; infected) and baseline fungal burden (<5 log
_10_ CFU/ml; ≥5 log
_10_ CFU/ml).

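### EFA is to be compared between arms within HIV-status and fungal-burden subgroups of a 50-patient trial, which does not estimate whether the effect differs between subgroups

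*Protocol article*

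**What the plan says.** The section on analysis of the primary endpoint fixes a linear mixed model for log10 fungal counts, with left-censoring at the detection limit, random patient intercepts and slopes, and a treatment-by-time interaction. That interaction is the EFA contrast itself.

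The section then lists the comparisons: "Based on this model, EFA will be compared between the two treatment arms in all patients", in the per-protocol population, and in "subgroups defined by HIV status (uninfected; infected) and baseline fungal burden", with burden cut at 5 log10 CFU/ml. No other interaction is named. The subgroup comparisons stand in the same sentence as the intention-to-treat comparison, without qualification. Elsewhere the article does mark comparisons as informal: adverse events, and visual acuity under the other secondary outcomes.

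Randomization uses "stratification by hospital of enrolment and by HIV infection status". Power is given for the whole trial only: "n=25 subjects per group provide 80% and 90% power to detect a difference in EFA of -0.11 or -0.13 log10CFU/ml/day, respectively".

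**The concern.** The usual reason for analysing EFA by HIV status and by baseline burden is to see whether tamoxifen works better or worse in one kind of patient. That is a question about the difference between two slope differences. Comparing the arms inside each subgroup answers another question: whether an effect can be detected there, given that subgroup's size.

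The trial has 80% power at -0.11 only when all 50 patients are used. Each subgroup has less, and the smaller one often much less. A pattern of significance in one subgroup but not the other is then an ordinary result of a common effect, yet it is easily read as effect modification. HIV status is particularly open to this. The article expects different infecting strains in patients without HIV, so a chance split would have a ready biological explanation.

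At stake is the reading of the subgroup results. The primary intention-to-treat comparison is not affected.

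**Working it through.** **Inputs**

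- Size and allocation: "50 patients will be recruited providing" (Abstract); "Randomization will be 1:1 to either Tamoxifen augmented or standard antifungal therapy" (Randomization).
- Stated power at 25 per arm: 80% at -0.11 and 90% at -0.13 (Sample size and power considerations).
- Significance level: not stated. The section says only that the simulations "determined the proportion of significant results (i.e. the estimated power". Assumed two-sided 0.05.
- Standard error of the EFA difference: not stated, because power came from resampling earlier patients and "simulating this treatment effect on top of the observed fungal count measurements". It is back-calculated here.
- Subgroup sizes: not stated. Splits from 50:50 to 80:20 are assumed.
- Equal variance in the subgroups and 1:1 allocation within each are assumed.

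**Step 1: consistency with the plan's own figures.** From 80% power at -0.11, SE = 0.11 / (1.960 + 0.842) = 0.0393. This predicts power at -0.13 of Φ(0.13/0.0393 − 1.960) = 91.2%, against 90% stated. In reverse, 90% at -0.13 gives SE = 0.13 / (1.960 + 1.282) = 0.0401 and 78.3% power at -0.11, against 80% stated. Both agree within 2 points, so one SE describes the stated power adequately. The resampling itself cannot be repeated without the earlier patients' data.

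**Step 2: power within a subgroup.** If the subgroup holds a fraction f of the patients, SE_f = 0.0393/√f and power = Φ(0.11/SE_f − 1.960).

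**Step 3: discordance.** The two subgroups share no patients, so their results are independent. With powers p1 and p2, the probability that exactly one is significant is p1(1 − p2) + p2(1 − p1).

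| Split | p1 | p2 | Exactly one significant, at -0.11 | Same, at -0.13 |
|---|---|---|---|---|
| 50:50 | 0.508 | 0.508 | 50% | 46% |
| 60:40 | 0.583 | 0.425 | 51% | 48% |
| 70:30 | 0.650 | 0.335 | 55% | 53% |
| 80:20 | 0.707 | 0.240 | 61% | 63% |

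(p1 and p2 are the powers at -0.11.) For example, at 70:30: 0.650 × 0.665 + 0.335 × 0.350 = 0.432 + 0.117 = 0.55.

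A simulation of 40,000 trials with t-tests on patient slopes gave 50-62% at -0.11 over about the same splits. At a one-sided 0.05 level the range is 50-59%.

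**Step 4: other true effects, 50:50 split.** The discordance is 2p(1 − p):

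- no effect: 2 × 0.05 × 0.95 = 9.5%
- -0.05: 2 × 0.145 × 0.855 = 25%
- -0.16: 2 × 0.822 × 0.178 = 29% (55% at 80:20)

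**Step 5: opposite signs.** At -0.11 and 50:50, each estimate has the wrong sign with probability Φ(−1.981) = 0.024, so the signs differ in 2 × 0.024 × 0.976 = about 5% of trials. At 80:20 the figure is 11%.

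**Step 6: the interaction test.** Under a common effect, the simulated interaction test was significant in 4.8-5.2% of trials. At 50:50 its SE is 2 × 0.0393 = 0.0785. It therefore has 80% power only for a between-subgroup difference of 0.0785 × 2.802 = 0.22, twice the design effect. For a difference of 0.11 its power is Φ(0.11/0.0785 − 1.960) = 29%.

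**The case against.** The strongest objection is that this is an omission normally left to a statistical analysis plan, which is not shown. The subgroup plan is one clause. It does not say that separate models will be fitted, that subgroup P values will be set against each other, or that no interaction will be tested. A single model with subgroup-specific slopes would also fit the wording, and subgroup slope differences belong in any good report. This stands in part: a reader might infer that the investigators will claim a differential effect or will never test one, and the article says neither. The point rests on what is stated, namely between-arm comparisons within subgroups, on the same footing as the main analysis and with treatment by time as the only interaction.

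A second objection concerns consequences. A reader might infer that the subgroup results will decide which patients enter the mortality trial. The Abstract and Discussion say only that the results inform whether to proceed to a larger trial, and no aim concerns effect modification. That inference is not supported.

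A third is that the headline figure depends on assumptions, and it does (Step 4). Equal variance is also doubtful for the burden subgroups, since patients with low initial counts may reach the detection limit sooner and supply fewer quantified values.

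Finally, an interaction test in 50 patients will usually be inconclusive. That is true, and it is a reason to label the subgroup results exploratory. It does not make the within-subgroup tests informative about a difference.

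**Conclusion.** The point holds as a minor improvement to the analysis. The stated within-subgroup comparisons do not estimate whether the EFA effect differs by HIV status or baseline burden, and the article neither adds a contrast that does nor labels the comparisons exploratory.

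If the effect is common to both subgroups and near the design value of -0.11, exactly one subgroup is significant in about 50-61% of trials for splits from 50:50 to 80:20. An interaction test would wrongly signal a difference in about 5%. The 50-61% rests on a two-sided 0.05 level, equal variance and assumed subgroup sizes.

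Two stronger readings should be avoided. The subgroups do not disagree about half the time whatever the true effect: with equal subgroups the figure is 9.5% with no effect, 25% at -0.05 and 29% at -0.16. Nor does disagreement here mean estimates pointing in opposite directions, which at -0.11 happens in only about 5-11% of trials.

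**What to change.** For each of the two factors, extend the same censored mixed model with the subgroup, its lower-order terms and a treatment-by-time-by-subgroup term. Report the slope difference with its 95% confidence interval in each subgroup, and the interaction estimate with its 95% confidence interval. Label the subgroup results exploratory, and state that no conclusion about a differential effect will be drawn from within-subgroup P values.

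The cost is two extra model fits, with no new data. The interaction test has low power, about 29% for a between-subgroup difference of 0.11 at a 50:50 split, and the plan should say so, so that a non-significant interaction is not read as evidence of a uniform effect. If an existing analysis plan already contains this contrast, a sentence in the article pointing to it is enough.

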## Analysis of secondary endpoints

### Survival until 10 weeks after randomization

Overall survival will be visualized using Kaplan-Meier curves and modeled using the Cox proportional hazards regression model with stratification by HIV status. In addition, survival will be modeled with a multivariable Cox regression model including the following covariates in addition to the treatment group: baseline log
_10_-fungal load, Glasgow coma score less than 15 (yes or no), HIV infection status, and ARV treatment status at study entry (naïve or experienced).

### Disability at 10 weeks.

The disability score at week 10 follow-up is defined as the higher (worse) of “ the two simple questions” and the Rankin score assessed at that time point, and will be categorized as good outcome, intermediate disability, severe disability, or death (in case the patient died before 10 weeks) as previously described
^45^. The ordinal 10-week score (“good”>”intermediate”>”severe”>”death”) will be compared between the two arms with a proportional odds logistic regression model depending on the treatment arm and HIV infection status. The result will be summarized as a cumulative odds ratio with corresponding 95% confidence interval and p‐value. Patients lost to follow up will be analyzed according to their last recorded disability status. If the rate of patients lost to follow-up exceeds 10%, we will also perform an alternative analysis based on multiple imputation of missing values.

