### Secondary aims

The secondary aims are to

-demonstrate the proof of concept that Tamoxifen can be safely administered with amphotericin and fluconazole to generate preliminary data that will support a larger phase 3 trial of Tamoxifen in cryptococcal disease-determine the effects on survival and disability at 10 weeks following study treatment initiation,-define the pharmacokinetics of amphotericin, fluconazole and Tamoxifen in blood and CSF-better understand the pathogenesis of cryptococcal meningitis through defining the species, subtype, drug susceptibility and in situ gene expression of the infecting
*Cryptococcus* and host response

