## Endpoints

### Primary endpoint

The primary outcome is Early Fungicidal Activity (EFA), i.e. the rate of clearance of yeast from cerebrospinal fluid, over the first 2 weeks following randomisation. Repeated lumbar punctures are part of routine care for cryptococcal meningitis in order to identify and manage raised intracranial pressure and to determine the response to treatment. In this trial, lumbar punctures are scheduled on days 1, 3, 7, 14, and additionally as clinically indicated. Whenever a lumbar puncture is performed we will determine the amount of viable yeast in CSF through culture. Based on the patients’ longitudinal quantitative yeast count measurements, EFA will be determined as described in the statistics section. Higher EFAs have been associated with better outcomes (survival and disability) in Vietnamese patients with cryptococcal meningitis
^8,
9^.

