***Visual deficit at 10 weeks.*** Visual deficit occurs in 5–40% of patients with cryptococcal meningitis depending upon underlying immune status
^5,
8^. The pathogenesis is unclear. We will compare the incidence of blindness and other visual deficit between treatment groups. Visual deficit will be assessed using a simple 6 point scale, as used in previous studies (see
Table 3).

***Time to new neurological event or death until 10 weeks.*** A neurological event is defined as a fall in Glasgow coma score by ≥2 points for ≥2 days from the highest previously recorded Glasgow coma score (including baseline) or the occurrence of any of the following adverse events: cerebellar symptoms, coma, hemiplegia, paraplegia, seizures, cerebral herniation, new onset blindness or deafness, or cranial nerve palsy.

***Longitudinal measurements of intracranial pressure during the first 2 weeks.*** Intracranial pressure (ICP) will be measured at study entry, day 3, 7, and 14, and if clinically indicated (depending on local practice). The main outcomes are longitudinal ICP-measurements until day 14.

Clinical need and local practice will determine the frequency of lumbar punctures post day 14 and clinician’s diagnoses of raised ICP based upon the presence of headache, nausea, diurnal and postural variation, relief with lumbar puncture and presence of papilloedema. Thus, these measures will only be descriptively analyzed.

***CD4 count at 10 weeks.*** CD4 count measurement is indicated in HIV infected patients, and CD4 lymphopenia has been described in HIV uninfected patients with cryptococcal meningitis. Moreover, Tamoxifen may reduce CD4 cell apoptosis which may be beneficial
^47^.

***Blood and CSF concentrations of amphotericin, Tamoxifen and fluconazole.*** Pharmacological data on antifungal drugs are lacking. Dosing has been inferred from studies in healthy volunteers, or patients with other diseases. There are no studies of combination therapy at the doses currently recommended
^48–

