### Screening

Only patients who are 18 years or older, who are not known to be pregnant, and who have at least one of positive CSF or blood/serum/plasma/urine LFA test, positive blood or CSF culture, or positive CSF microscopy will be consented. Consented patients will undergo the following screening procedures/tests. In the case of an unconscious patient, information will be obtained from a knowledgeable relative or caregiver.

- Medical history will be taken including: 1) signs and symptoms consistent with cryptococcal meningitis, 2) allergy to Tamoxifen, 3) history of breast or uterine cancer, venous thromboembolic events and > 4 days anti-fungal therapy.

- All females of child bearing age will have a urine or blood pregnancy test.

- 12 lead ECG to exclude cardiac conduction defects

- Creatinine level.

- HIV status will be confirmed from clinical history or testing as per standard of care. HIV testing is indicated and part of routine care for all patients with cryptococcal meningitis, since it defines the need for antiretroviral therapy and prophylaxis against other opportunistic infections.

- A lumbar puncture will be performed on all patients to obtain CSF. The opening CSF pressure will be determined using a spinal manometer. CSF will be tested by: 1) India ink stain or equivalent, 2) quantitative culture, 3) lateral flow cryptococcal antigen test. Cultured isolates will be stored for subsequent studies. Residual CSF will be stored for cryptococcal gene expression studies which will be done in patients who pass screening and enter the full study.

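### The 10-week disability comparison has no analysis adjusted for baseline coma score and fungal load, although both are collected and used in an additional survival model

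*Protocol article*

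**What the plan says.** **Disability.** Under the analysis heading Disability at 10 weeks, the four-level score (good, intermediate, severe, death) is compared "with a proportional odds logistic regression model depending on the treatment arm and HIV infection status". No other covariate and no second model is given.

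**Survival.** Two analyses are planned. The first-listed is "modeled using the Cox proportional hazards regression model with stratification by HIV status". Then: "In addition, survival will be modeled with a multivariable Cox regression model", whose covariates besides arm are baseline log10 fungal load and "Glasgow coma score less than 15 (yes or no), HIV infection status, and ARV treatment status at study entry".

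**Related endpoints.** Time to new neurological event or death is analysed like overall survival, so it also gets an additional adjusted model. The QTc-change and CD4 analyses adjust for HIV status and the outcome's own baseline value.

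**Availability.** A baseline coma score is presupposed by the neurological-event definition, which counts a fall "from the highest previously recorded Glasgow coma score (including baseline". For fungal load, the Screening section states: "CSF will be tested by: 1) India ink stain or equivalent, 2) quantitative culture, 3) lateral flow cryptococcal antigen test".

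**Status.** Disability is paired with survival in a secondary aim: "determine the effects on survival and disability at 10 weeks following study treatment initiation". The primary endpoint and the sample size concern early fungicidal activity. No power is stated for disability.

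**The concern.** Deaths by 10 weeks form the worst category of the disability score. In the Background, 33% of patients on amphotericin-fluconazole had died by 10 weeks, so mortality makes up a large part of the ordinal outcome. The protocol considers coma score and fungal load worth adjusting for when the outcome is death, and again when it is neurological event or death. It gives no reason for leaving disability without such an analysis.

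Two things are at stake. One is efficiency: strong baseline predictors left out of a proportional odds model cost power. The other is chance imbalance. Randomization is stratified by hospital and HIV status, not by coma score or burden. With 25 patients per arm a sizeable difference in coma score is not rare, and the only planned disability odds ratio would carry it. An adjustment added after seeing the imbalance would be post hoc.

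**Working it through.** **1. The plan's own power figure.** There is none for disability. The only stated figures are for early fungicidal activity with n = 25 per arm: 80% power at a difference of 0.11 and 90% at 0.13 log10 CFU/ml/day. They come from resampling patient data, so they cannot be rebuilt from the text. They can be checked against each other with a normal approximation (two-sided 5%, assumed):

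- Implied SD = 0.11 × √(25/2) / (1.960 + 0.842) = 0.139.
- Power at 0.13 = Φ(0.13 / (0.139 × √(2/25)) − 1.960) ≈ 91%.

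The two figures agree, and nothing below changes them.

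**2. Average power for disability.** Trials of 50 patients (25 per arm) were simulated from a proportional odds model. Two models were compared by likelihood-ratio test at 0.05: arm + HIV, and arm + HIV + GCS<15 + log10 fungal load. There were 1,500 runs per setting, so the simulation error is about 1.3 points per figure near 50%.

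From the document: 33% deaths. Assumed: good 30%, intermediate 20%, severe 17%; GCS<15 in 35%; 80% HIV infected with no HIV effect; fungal-load SD 1.3 log10; and all prognostic odds ratios.

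| Prognostic OR: GCS<15 / per log10 | Treatment OR 2: arm + HIV → extended | Treatment OR 3: arm + HIV → extended |
|---|---|---|
| 1 / 1 (none) | 28% → 30% | 55% → 55% |
| 2 / 1.3 | 28% → 30% | 52% → 55% |
| 3 / 1.5 | 24% → 28% | 50% → 57% |
| 5 / 2.0 | 20% → 26% | 40% → 52% |

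With no treatment effect, rejection was 5.1–6.0% for arm + HIV and 5.8–6.9% for the extended model. A small part of the apparent gain is therefore small-sample inflation.

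**3. Other assumptions.** Here the categories were 30/22/15/33%, GCS<15 was present in 40% with OR 4, and fungal load had SD 1.2 with OR 1.5 per log10. With 3,500 runs, power went from 46% to 54% at treatment OR 3 and from 63% to 71% at OR 4. A separate run of 2,000 gave 45% to 53% at OR 3, with null rejection of 6.3% and 7.5%.

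**4. Chance imbalance.** Take GCS<15 in 40% (assumed) and independent Binomial(25, 0.4) counts in the two arms. They differ by at least 5 patients in 19% of trials and by at least 6 in 11%, counting both directions. With the assumptions of step 3, counts fixed at 13 against 7, and 2,000 runs:

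| True OR | Arm with more GCS<15 | Arm + HIV: median OR, rejection | Extended: median OR, rejection |
|---|---|---|---|
| 3 | Tamoxifen (13 v 7) | 1.95, 23% | 3.19, 50% |
| 3 | Control (7 v 13) | 3.74, 69% | 3.28, 52% |
| 1 | Tamoxifen (13 v 7) | 0.70, 10% | 0.95, 7% |

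The arm + HIV estimate moves with the imbalance in either direction. The extended model stays near the true value.

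**The case against.** **The survival parallel is weaker than it looks.** A reader might infer that the protocol adjusts survival for coma score and fungal load and then contradicts itself on disability. The text does not support that. The first-listed survival analysis uses HIV status only, as the disability model does, and the four-covariate model is an addition. What is missing is a matching additional analysis.

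**Nothing in the disability model is invalid.** HIV status is a stratification factor, and adjusting for it in a prespecified model controls type I error over all randomizations. The distortion in step 4 of the working is conditional on imbalance; averaged over randomizations it cancels, and the confidence interval already allows for it. An odds ratio nearer 1 without covariates is partly non-collapsibility: the two models estimate different quantities. All this stands.

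**The endpoint is secondary and the gain is modest.** A reader might infer that material power on a main clinical outcome is thrown away. Disability is one of about a dozen secondary endpoints, with no power claimed. Only the 33% mortality comes from the document. With weak predictors the gain is about 2 to 3 points. This also stands.

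**Supporting analyses can be left to an SAP.** This carries less weight, because the protocol states the disability covariates outright and lists the adjusted survival model at the same level of detail.

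**Baseline counts may be missing or below the detection limit.** The Screening section lets some patients be randomized without a further lumbar puncture. That is a real cost, but the adjusted survival model and the fungal-burden subgroups already face it.

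**Conclusion.** The point holds as an inexpensive improvement to a valid plan. It does not identify an error or a contradiction. The disability comparison lacks any analysis adjusted for two baseline predictors that the protocol collects and uses for survival.

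If the predictors are prognostic, the expected gain is about 2 to 6 points of power at a treatment odds ratio of 2 and 3 to 12 points at 3. The upper ends need very strong predictors. At these effects power does not exceed about 57% with either model, so adjustment does not make disability a decisive endpoint. The firmer benefit is protection of the estimate when coma score is unbalanced, which at 25 per arm is a realistic possibility.

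The sizes rest on the assumed category shares, GCS<15 prevalence, fungal-load SD and prognostic odds ratios. The direction depends only on the covariates predicting disability.

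**What to change.** In the analysis section on disability at 10 weeks, prespecify a proportional odds model with treatment arm, HIV status, baseline Glasgow coma score below 15 (yes/no) and baseline log10 fungal load. Preferably make it the main disability analysis, with the arm + HIV model as supporting. At minimum, add it as an additional adjusted model parallel to the one for survival. The survival list also contains ARV status. Leaving it out keeps the model small, but the choice should be stated.

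Use one rule for missing and below-limit baseline counts in both the disability and the adjusted survival model, and write it down, since the protocol gives none for the survival covariate.

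Timing matters: the Trial status section reports enrolment complete and analysis under way. The change counts as prespecified only if it is fixed before disability results by arm are examined. Otherwise report the adjusted model as an unplanned supporting analysis.

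Cost: a sentence or two and no new data. The downsides are two more coefficients with 50 patients, slight small-sample inflation of the test (about 6 to 7.5% against 5 to 6% in the simulations), an odds ratio conditional on more covariates, and possibly a few patients without a baseline count.
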